**(IRAS Project ID 228214)**

*Background*

Workforce surveys in the United Kingdom suggest that between 25% and 40% of workers in various occupations would meet the diagnostic criteria for a minor psychiatric disorder (Hardy, Woods, & Wall, 2003; Stride, Wall, & Catley, 2007; Wall et al., 1997). In terms of cost, higher levels of employee distress have been associated with an elevation in

both sickness absence and work cutback days, where distressed employees are present at work but unable to perform effectively (Hardy et al., 2003; Kessler & Frank, 1997; Kessler, Merikangas, & Wang, 2008). In view of these observations, it is concerning that only a small fraction of distressed employees receive evidence -based interventions in or out of the workplace (Hilton et al., 2008; White, 2000). For example, Hilton et al. (2008) recently estimated that 78% of Australian workers with clinically significant distress were not currently receiving g any recognised support, and the picture seems to be similar in the UK workforce (White, 2000). Indeed changes in the organisation and the management of health care provision in the UK, coupled with the nature of medical practice have increased the experience of stress, burnout and poor psychological wellbeing in general practitioners and health professionals more generally (Gibson et al. 2015). Moreover, these high levels of distress are likely to have resultant implications for patient care (e.g., reduced patient safety and increased medical error) and for the health professionals’ health and wellbeing (Hall et al., 2016; [name] et al., 2000). Taken together, these findings underscore the importance of implementing and evaluating interventions that have the potential to improve mental health in the workplace, particularly within the NHS.

In order to prevent and reduce distress among employees, researchers have begun implementing and evaluating mindfulness-based worksite training interventions. One of these interventions is based on Acceptance and Commitment Therapy (ACT; Hayes et al., 1999). ACT is a mindfulness-based intervention that seeks to change the way people respond to stress- related thoughts and feelings. Unlike traditional stress management approaches (such as relaxation training), ACT does not seek to reduce employees’ unwanted thoughts and emotions. Instead, ACT increases psychological flexibility, which refers to the ability to pursue valued work and life goals even when experiencing difficult thoughts and emotions.

Previous pilot studies have suggested that several (at least three) half day sessions of training in ACT principles and techniques can lead to clinically meaningful reductions in employee distress and increases in levels of psychological flexibility. ACT interventions also appear to affect improvements in various other indicators of employee well-being, such as the ability to be innovative at work (Bond & Bunce, 2000; Dahl et al., 2004; Flaxman & Bond, 2006; 2010a; 2010b; Varra et al., 2008). Moreover, higher levels of psychological flexibility have been associated not only with improved mental health, but also with improved job performance and absenteeism in UK workers (Bond & Bunce, 2003; Bond, Flaxman, & Bunce, 2008).

To ascertain whether these beneficial effects of ACT might also apply to NHS primary care staff, this project will implement and evaluate an ACT -based worksite intervention for improving well-being, work-related mental health and patient safety in this group. The programs will be implemented in a brief form across four consecutive two hour sessions. This will be the first study evaluating the efficacy of an ACT-based workplace intervention in NHS primary care settings. Based on previous research, it is predicted that ACT will lead to significant increases in general well - being, work related mental health and psychological flexibility. In this study we will also assess whether there is a perceived positive influence on clinical practice, via improvements in safe clinical practice.

*Hypotheses*

1) Compared to a wait-list control group, those receiving ACT will have significantly better scores on primary and secondary outcome measures at post-intervention time-points.

2) Improvements in outcomes will be mediated by improvements in psychological flexibility.

**METHODS**

*Design*

The study will employ a randomised controlled design to examine the effectiveness of a group-based ACT training programme for improving the well-being of NHS staff, compared to a wait-list control group.

*Participants*

Participants will be primary care staff within the NHS in Leeds and West Yorkshire. There will be one inclusion criterion: currently employed by the NHS and working within NHS primary care settings in Yorkshire and Humber. There will also be one exclusion criterion: not presently at work.

Based on sample sizes from other ACT studies in similar settings (e.g., Flaxman & Bond, 2010; Flaxman et al., 2016) we aim to recruit 140 people.

*Procedure*

Recruitment: The study will be advertised to potential participants via local awareness raising in primary care settings. Participants will be given information about the study and will be given the e-mail address of a member of the research team (NHS e-mail) to contact a member of the research team if interested in opting-in to the study.

Once participants have expressed an interest in the study, they will immediately be sent the participant information sheet (PIS) via e-mail, which outlines the nature of the research and training. After having had at least 24 hours to consider the information presented in the PIS, consent will be taken online. A consent form will be the first sheet of the pre-intervention questionnaire. Immediately after giving consent participants will then enter demographic details and generate their own individual participant number (First two letters of their mother's maiden name initials and the last four digits of their telephone number). This reference number will be used to complete all online questionnaire batteries.

Participants will be informed that they will shortly be randomly allocated to begin the training, the first session beginning in late September 2017, or to the waitlist control group. As soon as an initial 40 people have volunteered, the first randomisation process will take place, allocating volunteers to the ACT training programme or to the waiting list control group. Participants allocated to the training group will then receive dates, times, and locations of the scheduled training sessions. Participants will be randomised to groups by the research team using a computer generated randomisation procedure.

Those allocated to the waiting list control will begin the training in Feb /March 2018. These participants will receive an email (or letter) providing reasons for being allocated to the later training group (i.e., limitations on the number of people that can be trained at one time, and the need to rigorously evaluate the impact of the training on staff well - being). All participants will be required to complete an online questionnaire battery (described in more detail below) on four separate occasions over the 14 week evaluation period. They will be e-mailed the questionnaire at the appropriate time-point, if they don’t complete the questionnaire within three days, they will be sent a reminder e-mail.

*Intervention*

The intervention will be based on an existing standardised ACT protocol designed for workplace settings. Participants will be invited to attend a total of four two-hour group sessions; these sessions will occur on four consecutive weeks.

Each session will consist of between 8 and 15 people. Training sessions will be delivered by experienced clinicians, who are also trained mindfulness teachers either on the national register or who comply with the Good Practice Guidelines. These trainers will be taught to deliver the study’s ACT intervention over a minimum of two training days with [name], who has extensive experience training professionals to deliver workplace interventions based around ACT. They will be supervised by [name] and by a professional mindfulness supervisor.

*Measurement*

A questionnaire battery will be administered to participants on four occasions:

1. Pre-intervention: minus 1 to 2 weeks

2. Mid-intervention: between sessions 2 and 3 of the intervention (week 3)

3. Post-intervention: one week after session 4 (week 5)

4. Follow-up: 3 months after post-intervention (week 19)

The questionnaire battery will take approximately 25 minutes to complete on each occasion. These on line questionnaires will be completed via encrypted survey software (known as Bristol Online Surveys) hosted by the CI’s institution (University of Leeds). Each participant will receive an email containing a link to the questionnaires. Those allocated to begin the training in in September 2017 will be e-mailed the questionnaires to complete prior to training.

*Primary outcome*

1. General Health Questionnaire 12 (Goldberg & Williams, 1988). The GHQ-12 is one of the most widely used and well-validated measures of general well-being/mental health among working populations. The scale consists of a mix of positively and negatively worded items designed to capture various aspects of a person’s recent psychological functioning (e.g., sleep loss due to worry, ability to play a useful part in things, feeling able to face up to problems).

Higher scores indicate a higher level of psychological distress. As well as providing a primary overall measure of general mental health, the GHQ-12 can also be used to indicate the proportion of the sample that is experiencing clinically relevant level of distress.

*Secondary outcomes*

2. Shirom-Melamed Burnout Measure (SMBM; Shirom, 2003; Shirom & Melamed, 2006). The SMBM will be used to measure job-related burnout. This well-established 14-item scale has three subscales that are designed to capture core components of the burnout syndrome: physical fatigue, emotional exhaustion, and cognitive weariness. We selected this particular measure for the following reasons: (1) its theoretical underpinnings are clearly specified

(Shirom, 2003); (2) it explicitly seeks to capture a construct that is distinct from depression and anxiety; and (3) unlike more generic burnout measures, responses to the SMBM are temporally anchored to the past 30 work days.

3. Work-related worry and rumination during non-work time. Maladaptive perseverative cognition will be measured with the affective rumination subscale of the work-related rumination questionnaire (WRRQ; Cropley, Michalianou, Pravettoni, & Millward, 2012). This 5-item scale captures the degree to which a person is troubled by intrusive work-related thoughts during their leisure time. This subscale has demonstrated good psychometric properties among various samples of UK workers (Cropley et al., 2012; Querstret & Cropley, 2012). This measure will be supplemented with a 5-item work related worry and rumination scale developed and validated by Flaxman and colleagues (Flaxman, 2014; Flaxman et al., 2012). Participants will be asked to report amount of work-related worry/ rumination experienced during non-work time (e.g., evenings and weekends) over the past week.

4. Perceptions of patient safety will be measured using the safe practitioner measure using the following two items “In the past four weeks, my practice is not as safe as it could be because of work related factors/conditions” and “My practice is safe”. This measure has been shown to bereliable and valid (Louch et al., in press; Louch et al., 2016).

*Process of change measures*

1. Multidimensional Experiential Avoidance Questionnaire (MEAQ) – Distress Endurance subscale (Gamez et al., 2011). The 11-item MEAQ-DE subscale measures an important aspect of psychological flexibility: one’s ability to endure difficult thoughts and feelings in order to complete important activities.

2. 15-item Five Facet Mindfulness Questionnaire (Gu et al., 2016; Baer et al., 2006, 2008). This is the recent 15-item reduction (Gu et al., 2016) of the popular 39-item scale (Baer et al., 2006, 2008), which is the most widely used multidimensional measure of mindfulness skills. The FFMQ has 5 subscales: observing (e.g., “When I’m walking, I deliberately notice the sensations of my body moving”); describing (labelling with words; e.g., “I’m good at finding the words to describe my feelings”); acting with awareness (e.g., “I find it difficult to stay focused on what’s happening in the present”); nonjudging of experience (e.g., “I make judgments about whether my thoughts are good or bad”); and nonreactivity to difficult inner experience (e.g., “When I have distressing thoughts or images, I am able just to notice them without reacting”).

3. Valuing Questionnaire (VQ; Smout et al. 2014). The 10-item valuing questionnaire is designed to assess people’s ability to engage in action that is consistent with their personal values, and also their experiences of obstacles to pursuing such actions. The scale has previously demonstrated good psychometric properties in both clinical and nonclinical adult populations.

4. Self-Compassion Scale – short-form (SCS-SF; Raes et al., 2011). This 12-item self-compassion scale has 6 subscales: self-kindness; self-judgement; common humanity; isolation; mindfulness; and over-identification. The measure captures the propensity to treat oneself with care and kindness, to accept one’s imperfections, and tendency

to take a balanced perspective on one’s experiences. We included this scale due to the growing interest in self-compassion as a potential mechanism of change in ACT (and other mindfulness-based) interventions, and the relevance of self/other compassion for professionals (such as GPs) working in healthcare settings (e.g., Cummings, 2014).

*Other measures*

Demographics questionnaire (age, gender, occupation, years in occupation, previous/current mindfulness practice).

*Analyses*

Hypothesis 1: Compared to a wait-list control group, those receiving ACT will have significantly better scores on outcome measures at all post-intervention time-points.

Here we will compare group scores between the control and ACT conditions at all time points using ANOVA. All available data will be included in the analyses, regardless of number of treatment sessions attended. This will involve an intention-to-treat (ITT) approach, with imputation of missing data by last value carried forward.

Hypothesis 2: Improvements in outcomes will be mediated by improvements in psychological flexibility in the ACT condition but not in the wait-list control condition. Here we will use mediation and moderation analysis to test whether change in the psychological flexibility processes helps to explain any changes in outcome variables. We will run this analysis to test if these effects are specific to the intervention group.

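### The stated 14-week evaluation cannot hold four questionnaires running to week 19, and wait-list training is fixed by calendar rather than tied to each batch's completed follow-up

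*Protocol*

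**What the plan says.** All of this is in the Protocol, METHODS.

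- **Participants:** "we aim to recruit 140 people".
- **Procedure, randomisation:** "As soon as an initial 40 people have volunteered, the first randomisation process will take place". Later randomisations are implied, but neither their number nor their dates are given. For those allocated to immediate training, the protocol gives "the first session beginning in late September 2017".
- **Procedure, wait-list:** "Those allocated to the waiting list control will begin the training in Feb /March 2018". One window is given for all controls.
- **Procedure, evaluation:** the questionnaire battery is completed "on four separate occasions over the 14 week evaluation period".
- **Measurement:** the four occasions are "Pre-intervention: minus 1 to 2 weeks"; a mid-intervention point in week 3; "Post-intervention: one week after session 4 (week 5"; and "Follow-up: 3 months after post-intervention (week 19".
- **Analyses:** Hypothesis 1 is tested by comparing the arms at every time point with ANOVA, on an intention-to-treat basis with last-value carry-forward. Week 19 is therefore one of the between-arm comparisons.

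Nothing in the protocol makes a control's training wait for that person's week 19 questionnaire, and nothing gives later batches their own wait-list date.

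**The concern.** There are two linked problems. First, the stated evaluation length and the questionnaire schedule cannot both be right. Staff who counted 14 weeks from baseline would send the last questionnaire well short of three months after the intervention.

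Second, the wait-list arm is an untreated comparator only until its members are trained. Follow-up moves with each batch's start, while the wait-list window stays fixed in the calendar. The later a batch starts, the more likely its controls are to have had some or all of the training when they give their week 19 score. If the training helps, the week 19 contrast shrinks toward zero, and the trial loses its evidence on whether the benefit lasts. Analysis cannot recover the untreated value once a control has been trained.

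**Working it through.** **1. Length of the schedule.** Post-intervention is one week after session 4 and is labelled week 5. Session 4 is therefore week 4 and session 1 is week 1.

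- Session 1 to week 19: 19 − 1 = 18 weeks (126 days).
- Baseline, 1 to 2 weeks before session 1, to week 19: 18 + 1 = 19, or 18 + 2 = 20 weeks. If minus 1 to 2 is read as a week label, 19 − (−1) = 20, or 19 − (−2) = 21.
- Post-intervention to follow-up: 19 − 5 = 14 weeks.

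The stated 14 weeks is reproduced only by the last interval, which holds two of the four occasions. No reading that covers all four gives 14.

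If 14 weeks were counted from baseline, the last questionnaire would fall 14 − 1 = 13 or 14 − 2 = 12 weeks after session 1. Post-intervention is 4 weeks after session 1, so that is 9 or 8 weeks after post-intervention. A smaller mismatch: three months is about 13 weeks, which from week 5 gives week 18 rather than 19.

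**2. The dated start.** Week 19 = session 1 + 126 days.

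| Session 1 | Week 19 |
|---|---|
| 18 Sep 2017 | 22 Jan 2018 |
| 25 Sep 2017 | 29 Jan 2018 |
| 29 Sep 2017 | 2 Feb 2018 |

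Against a wait-list start on 1 February, the margin runs from 10 days to none.

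**3. Later starts.** The latest session 1 for which week 19 is no later than the wait-list start is that start minus 126 days.

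| Wait-list training begins | Latest session 1 |
|---|---|
| 1 Feb 2018 | 28 Sep 2017 |
| 1 Mar 2018 | 26 Oct 2017 |
| 31 Mar 2018 | 25 Nov 2017 |

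For starts between 28 September and 25 November, overlap depends on where in the window the controls actually begin. A batch starting on 27 November reaches week 19 on 2 April, after the whole window.

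**4. Part-trained or fully trained.** Four weekly sessions from 1 February end on 22 February. Controls would have finished the course before week 19 only if their batch started after 22 February − 126 days = 19 October. For a 1 March start, the course ends on 22 March and the cut-off is 16 November.

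**5. Other time points.** Week 5 is session 1 + 28 days. It passes 1 February 2018 only for batches starting after 4 January 2018, so weeks 3 and 5 are not exposed for autumn starts.

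**6. Illustration of the loss.** None of these inputs is in the protocol: 70 per arm (equal allocation of 140, no dropout), two-sided 5%, a true standardised difference d, and a share f of controls who gain the full effect before week 19. The contrast becomes d(1 − f), and power ≈ Φ(d(1 − f)√(70/2) − 1.96).

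| d | f = 0 | f = 25% | f = 50% | f = 50/70 |
|---|---|---|---|---|
| 0.3 | 42.7% | 26.5% | 14.2% | 7.3% |
| 0.5 | 84.1% | 60.2% | 31.5% | 13.2% |
| 0.7 | 98.5% | 87.4% | 54.4% | 21.9% |

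The last column is an extreme. It needs every control outside the first batch (140 − 40 = 100 people, about 50 controls) to be fully trained before follow-up.

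**The case against.** The strongest reply is that the only dated schedule works. The protocol names one start for immediate training and one later window for the wait-list, and on those dates week 19 falls essentially before the window opens. A later randomisation need not mean a later training start, and the Feb/March window may have been meant for the first batch only. The window is also two months wide, so it leaves room to stagger control groups. The 14 weeks may simply be the post-intervention to follow-up interval, and the numbered list under Measurement is explicit.

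Much of this stands. A reader might infer that one fixed training date applies to every control, or that later-batch controls will in fact be trained before follow-up. The documents support neither: the protocol gives a window, and it gives no later start dates. The large power losses in step 6 likewise cannot be read as expected losses.

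Two things remain. The 14-week figure is attached to all four occasions, so the text is wrong as written whatever was meant. And the sequence that protects the control arm at week 19 rests on how the dates happen to fall, because no rule requires it. Staggered starts are plausible: with groups of 8 to 15, 70 immediate-training participants need at least five groups (70/15 = 4.7), and the protocol itself cites limited training capacity as a reason for the wait-list.

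**Conclusion.** The concern holds in a limited form and should be fixed. The conflict between 14 weeks and a 19 to 20 week schedule is certain and rests on the protocol's own week numbers. Exposure of the week 19 comparison is possible but not shown. It is little or none if all training starts by late September 2017, depends on the actual wait-list date for starts between 28 September and about 25 November, and is certain for later starts if controls begin within the stated window.

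Only follow-up is at risk for autumn starts. The bias, assuming the training helps, is toward no difference, so it would weaken the evidence for a lasting benefit rather than create a false one. The size cannot be fixed from the protocol, because later start dates, allocation ratio and expected effect are not given.

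**What to change.** 1. Replace the 14-week figure under Procedure with the span that the Measurement schedule requires, and settle whether follow-up is week 19 or exactly three months after post-intervention.
2. Define week 19 from each batch's own session 1, for both arms.
3. Replace the single Feb/March 2018 window with a rule that each batch's wait-list training is scheduled after that batch's week 19 questionnaire, and that a control's questionnaire is collected before that person's first session.
4. If a control score is still returned after training began, keep the participant in the intention-to-treat analysis as randomised, report how many such scores there are, and add a sensitivity analysis that treats them as missing. Under the protocol's carry-forward rule an earlier score would then stand in, and the report should say so.

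Whole batches should not be dropped from the follow-up comparison. That would exclude randomised people against the protocol's own intention-to-treat statement, and in the extreme could remove 100 of 140. Nor should the remedy lean on a mixed model, which the protocol does not contain.

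The cost is protocol wording and scheduling of questionnaire e-mails. The one real downside is that wait-list training for later batches may begin after February/March 2018.

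### ACT is taught in groups of 8 to 15, but the planned ANOVA has no training-group term; if outcomes within a group are positively correlated, its standard error is too small

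*Protocol*

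**What the plan says.** The relevant statements are all in the Methods section of the protocol.

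- **Randomisation (Procedure).** The unit is the individual: "Participants will be randomised to groups by the research team using a computer generated randomisation procedure".
- **Sample size (Participants).** "we aim to recruit 140 people", justified by precedent: "Based on sample sizes from other ACT studies in similar settings". No allowance for clustering is stated.
- **Delivery (Intervention).** "Participants will be invited to attend a total of four two-hour group sessions; these sessions will occur on four consecutive weeks". Group size is fixed: "Each session will consist of between 8 and 15 people". There is more than one trainer, number not stated: "Training sessions will be delivered by experienced clinicians".
- **Control arm (Procedure).** "Those allocated to the waiting list control will begin the training in Feb /March 2018". Until then these participants belong to no training group.
- **Analysis of Hypothesis 1 (Analyses).** "Here we will compare group scores between the control and ACT conditions at all time points using ANOVA". The section adds intention to treat and last value carried forward.

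Nowhere does the protocol mention training group or trainer as a factor, an ICC, a random effect, or a robust standard error.

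**The concern.** People trained together share a trainer, a venue, dates and the dynamics of the group, so their scores after training may resemble each other. This can happen only in the ACT arm, which makes the design partially nested: clustered in one arm, independent in the other. An ANOVA of individuals by condition assumes independence in both. A repeated-measures version would handle correlation between one person's scores over time, but not correlation between members of the same training group.

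The comparison concerned is the test of Hypothesis 1, which covers the GHQ-12 as primary outcome and every secondary outcome. With roughly 70 ACT participants in only 5 to 8 groups, a few groups that did unusually well or badly could move the arm mean by more than the ANOVA allows for.

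**Working it through.** **The plan's own figure.** The target of 140 cannot be reproduced, because no effect size, SD, power or significance level is given. For reference, with 70 per arm, independence, two-sided 5% and 80% power (all assumed), the detectable difference is about 0.48 SD.

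**Inputs**
- From the protocol: N = 140; group size m = 8 to 15.
- Assumed: 1:1 allocation, so 70 per arm (the ratio is not stated); equal total variance in both arms; ICC 0.01 to 0.10 (none is given).
- Number of ACT groups: 70/15 = 4.7 and 70/8 = 8.75, so about 5 to 8.

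**Formulas**
- ACT-arm design effect: DE = 1 + (m − 1) × ICC.
- True over naive standard error of the difference, with only one arm clustered: r = √((DE + 1)/2).
- Actual error of the nominal 5% test: 2 × [1 − Φ(1.96/r)].
- Effective ACT-arm size: 70/DE.

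**Results**

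| m | ICC | DE | r | Actual error | Effective ACT size |
|---|---|---|---|---|---|
| 8 | 0.01 | 1.07 | 1.02 | 5.4% | 65 |
| 8 | 0.05 | 1.35 | 1.08 | 7.1% | 52 |
| 8 | 0.10 | 1.70 | 1.16 | 9.2% | 41 |
| 12 | 0.02 | 1.22 | 1.05 | 6.3% | 57 |
| 12 | 0.05 | 1.55 | 1.13 | 8.3% | 45 |
| 12 | 0.10 | 2.10 | 1.25 | 11.5% | 33 |
| 15 | 0.01 | 1.14 | 1.03 | 5.8% | 61 |
| 15 | 0.05 | 1.70 | 1.16 | 9.2% | 41 |
| 15 | 0.10 | 2.40 | 1.30 | 13.3% | 29 |

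One line in full, for m = 12 and ICC 0.05: DE = 1 + 11 × 0.05 = 1.55; r = √(2.55/2) = 1.13; 1.96/1.13 = 1.74; error = 8.3%.

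**Check by simulation.** A two-sample test was run under a zero mean difference, with 70 per arm and 40,000 replicates per scenario. At ICC 0.01, 0.02, 0.05 and 0.10 the rejection rates were 5.5%, 5.8%, 7.1% and 9.9% with 8 groups of 8 or 9, and 5.7%, 6.3%, 8.7% and 12.8% with 5 groups of 14. At ICC 0 the rate was about 5%, so the excess comes from clustering alone.

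**Detectable effect once clustering is modelled.** Take ICC 0.05 and 6 groups, so m = 70/6 = 11.67.
- DE = 1 + 10.67 × 0.05 = 1.533.
- Standard error = √((1.533 + 1)/70) = 0.190 SD.
- Satterthwaite df = (1.533 + 1)² / (1.533²/5 + 1²/69) ≈ 13.
- With t quantiles on 13 df, the effect detectable with 80% power is about 0.58 SD.

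The same steps give 0.54 SD with 8 groups and 0.60 SD with 5.

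**The case against.** Several points on the other side are sound.

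- **The ICC is unknown and could be small.** The Intervention section describes a standardised programme with common trainer training and supervision, and the Confidentiality section plans adherence checks on recorded sessions. These should limit differences between groups. A reader might infer that the standard errors are certainly too small, or that 11% to 13% is the expected error rate. The protocol supports neither: both depend on an ICC it does not give, and the top figures need 0.10.
- **The null matters.** If ACT changed nobody's score, training groups would induce no correlation. Similarity that predates training does not by itself inflate the error rate under individual randomisation. The inflation arises when the mean ACT effect is zero but groups truly differ.
- **Trainer and group belong to the intervention.** A reader might infer that a trainer effect could pass for an ACT effect. The protocol defines the intervention as a group programme, so that goes too far. The valid concern is generalising beyond a few particular groups.
- **The analysis text is short, and a SAP not shown may add terms.** ANOVA can carry a nested random factor. Even so, the protocol names the method and the contrast and mentions no group or trainer term anywhere, so the method as stated does not fit the design.
- **The remedy has a price.** Scaling 0.48 SD by the standard-error ratio alone suggests about 0.54 SD for groups of 12. That ignores the few degrees of freedom, which bring the figure to about 0.58 SD with 6 groups.

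These points make the size conditional. They do not make an analysis that ignores training groups suitable for this design.

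**Conclusion.** The point stands in conditional form. The protocol combines one-arm clustering with an ANOVA that neither estimates nor allows for it. Given a positive within-group ICC, the stated standard error is too small, by an amount that is trivial at ICC 0.01 and material from about 0.05. Across ICC 0.01 to 0.10 and groups of 8 to 15, the ANOVA understates the standard error by about 2% to 23%. The conclusion about size rests on the assumed ICC range, 1:1 allocation, equal total variances, and a null of zero mean ACT effect with real differences between groups. The mismatch between design and analysis rests on none of these.

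**What to change.** - **Record** each ACT participant's training group against the reference number. The Confidentiality section links questionnaire data to that number alone, and the demographics list under Other measures does not include training group. The same section lets participants switch to another session on request; for anyone who does, use the group as allocated.
- **Replace the ANOVA** with a partially nested linear mixed model, or an equivalent: a random training-group effect in the ACT arm only, each wait-list participant as a singleton, and Satterthwaite or Kenward-Roger degrees of freedom. Allow arm-specific residual variances.
- **Report** the estimated ICC with its uncertainty.

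The cost is one identifier and a change of analysis wording; no session or questionnaire changes. The statistical price is a wider interval and a variance component estimated imprecisely from only 5 to 8 groups. At ICC 0.05 the detectable effect at 80% power becomes about 0.54 to 0.60 SD, and this should be acknowledged beside the target of 140.
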